### Objectives

2.1

The primary objective of this sub‐study is to explore the relationship between the use of the AI‐based application and several factors: the duration of wound assessment, dressing changes, and documentation; the nurse's task load; and adherence to guidelines. We will adjust for potential covariates such as wound severity, the nurse's professional experience, and the general workload of the shift. A secondary objective is to evaluate the accuracy of the AI predictions regarding wound type and classification in a clinical setting, as well as the usability of the AI‐based application and standard clinical documentation systems.

Our hypothesis, which we intend to test, is that the use of the AI‐based application will enhance the differentiation, assessment, and documentation of PI and IAD by reducing the time required for wound assessment, dressing changes, and documentation; lowering nurses’ task load; and improving guideline adherence.

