### Sample Size

2.6

Based on current methodologies, we performed an a priori sample size calculation using power analysis (Döring and Bortz 2016) with the G*Power 3 software (Faul et al. 2007). For this calculation, we assumed moderate effect sizes between dependent and independent variables (Cohen 1988), an alpha level of 0.05, and a power of 0.80. To test correlations between dependent variables (task load, time, guideline adherence) and four independent variables (use of the demonstrator, general load of the shift, professional experience, severity of wound) using multivariate models (multiple linear regression) under these assumptions, we will require a total of 85 nurses.

With a calculated sample size of 85 nurses and considering up to four independent variables, we anticipate obtaining meaningful results within a manageable timeframe and with the available resources. Accounting for a projected 10% dropout and missing rate, based on experiences from previous studies, we plan to recruit 95 nurses to ensure a sufficiently large sample for subsequent evaluation.

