### Analysis Plan

2.12

Once data collection is complete, we will use multiple linear regression models to examine the effects of the AI‐based digital system on the duration of wound assessment, dressing change, documentation, perceived task load, and guideline adherence. We will calculate an individual linear regression model for each dependent variable and incorporate potential covariates such as the nurses’ professional experience, wound severity, and the general load of the shift. Nominal and ordinal variables (use of the AI demonstrator, severity of the wound, general burden of the shift, and guideline adherence) will be dummy coded. We will then assess each model for linearity, homoscedasticity, and the absence of multicollinearity to satisfy the assumptions of linear regression. If these conditions are met, we will proceed with standard multiple linear regression, incorporating all independent variables as predictors. The f‐test will be used to examine the extent to which the independent variables predict the dependent variable, with R² indicating how much of the variance in the dependent variable can be explained by the independent variables. The t‐test will assess the significance of the predictors. To determine the specific contribution of the use of the demonstrator, we will calculate the explanatory power for both the full regression model and a reduced model without the demonstrator use variable, using the difference in explanatory performance to isolate the effect attributable to the demonstrator use. Datasets with missing socio‐demographic data for nurses, used only to describe the sample and not part of the statistical analysis, will still be included in the analysis. However, datasets with missing values for independent variables will be excluded entirely, and datasets with missing values for dependent variables will be excluded only from the specific model where the data is missing. The significance level is set at 0.05. As this is an exploratory study and a separate model is calculated for each dependent variable, no correction for alpha error is required. To analyze the interrater reliability of the observers, we will use Kendall's rank correlation coefficient (Kendall's tau). To determine the performance of the AI‐based application in the clinical setting, we will calculate its accuracy in predicting wound type and wound classification, using the on‐site assessment of a study team member as ground truth. Additionally, we will descriptively evaluate the usability of both the standard clinical documentation systems and the AI‐based application in terms of central tendency, variability, and distribution.

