Potential challenges in implementing the AI‐based application in a clinical setting include technical issues, such as ensuring full Wi‐Fi coverage, and meeting hygiene requirements, such as disinfecting tablets. Another common hurdle in technology intervention studies is user acceptance. However, in the realm of technologies that support nursing tasks, studies have shown high technology acceptance (Zöllick et al. 2020). We therefore anticipate high acceptance due to the simplification of wound care and documentation processes. To further enhance user acceptance, local wound experts and ward managers have been involved in the development of the application and will be key users during its implementation on the wards. Additionally, the implementation will be supported by comprehensive training measures to ensure safe use and handling of the application and AI predictions. This is crucial, especially when addressing incorrect or inaccurate predictions made by AI and the ethical challenges that arise in biomedical AI (Mittelstadt et al. 2016).

As this study is monocentric, focusing only on nurses at one university hospital, the external validity is limited. Another limitation is the constrained resources of the project, which preclude the use of a randomized study design and may introduce slight biases due to the consecutive and non‐randomized observation of control and intervention groups, as well as the absence of blinding. Moreover, the organization of information events and recruitment of nursing staff may heighten awareness of pressure injury and IAD care, potentially influencing care and documentation and thus the results of the study. Organizational delays, which are inevitable due to clinical processes, may also introduce bias. We also acknowledge that factors such as ward affiliation might influence outcomes, but were not included in this exploratory pilot study due to the complexity of the models required and the limited sample sizes. For this reason, only the most crucial factors, from an expert perspective, were included in the analysis.

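### The plan names the difference in R² as the demonstrator's effect, but that quantity has no sign or unit and cannot by itself answer the directional hypothesis

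*Protocol article*

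**What the plan says.** The Analysis Plan (2.12) fits a separate multiple linear regression for each outcome. Demonstrator use is a dummy-coded predictor, alongside professional experience, wound severity and the load of the shift. Three outputs are named:

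- an overall F-test, with R² "indicating how much of the variance in the dependent variable can be explained by the independent variables";
- for single predictors, the t-"test will assess the significance of the predictors";
- for the demonstrator specifically, the explanatory power of the full model and of "a reduced model without the demonstrator use variable", "using the difference in explanatory performance to isolate the effect attributable to the demonstrator use".

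The section names no regression coefficient, adjusted mean difference or confidence interval as the effect estimate.

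Objectives (2.1) states a hypothesis with a direction. The application is expected to improve care by "reducing the time required for wound assessment, dressing changes, and documentation", by lowering task load and by improving guideline adherence. The Discussion concedes that the design "may introduce slight biases due to the consecutive" and non-randomized observation of the two groups, and also names the absence of blinding.

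**The concern.** The question asked and the measure chosen do not match. The hypothesis asks whether time and load go down and adherence goes up, and a reader will want to know by how much. A difference in R² reports only what share of the outcome's variance the demonstrator term accounts for. It takes the same value whether the application saves or costs the same amount of time, and it is not in minutes or points.

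If the sentence is followed as written, the figure offered as the demonstrator's effect must be read together with another part of the output before anyone can tell benefit from harm. The plan does not say that this other part will be reported as an estimate.

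The word *isolate* also claims more than the design can give. The demonstrator term is the phase term, so it carries whatever else differs between the two periods.

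**Working it through.** **The plan's own figure.** Sample Size (2.6) gives four predictors, "an alpha level of 0.05, and a power of 0.80", and says "we assumed moderate effect sizes between dependent and independent variables". Taking moderate as f² = 0.15 (an assumption, since the article gives no number), the overall F-test with 4 and N − 5 degrees of freedom and noncentrality f²·N has power 0.803 at N = 85 and 0.797 at N = 84. The stated 85 is therefore reproduced, and 85/0.9 = 94.4 rounds up to the 95 to be recruited. This check confirms the regression framework but does not decide the present point.

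**Sign, in closed form.** Assume a 50:50 split and no other predictors. A standardized difference d between phases gives

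- f² = d²/4
- ΔR² = f²/(1 + f²)

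For d = −0.5 (a saving), f² = 0.25/4 = 0.0625 and ΔR² = 0.0625/1.0625 = 0.059. For d = +0.5 (a cost), d² is the same, so ΔR² is again 0.059. Only d² enters, so the sign is lost.

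**Sign and unit, in the planned model.** Invented data were used: N = 85 (43 and 42 per phase), the demonstrator indicator plus three continuous covariates, and least squares with and without the indicator. The effect was set to −4 and then +4 minutes, and the outcome was expressed in minutes and then in seconds.

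| Effect built in | Unit | ΔR² | Coefficient (95% CI) | t |
|---|---|---|---|---|
| saves 4 min | minutes | 0.150 | −4.0 (−6.03 to −1.97) | −3.93 |
| saves 4 min | seconds | 0.150 | −240 (−361.52 to −118.48) | −3.93 |
| costs 4 min | minutes | 0.150 | +4.0 (1.97 to 6.03) | +3.93 |
| costs 4 min | seconds | 0.150 | +240 (118.48 to 361.52) | +3.93 |

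The R² difference is the same in all four rows. The coefficient, its interval and the sign of t are what tell them apart.

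**What the R² difference adds as a test.** F-change = ΔR² / [(1 − R² full)/(N − 5)]. With ΔR² = 0.1496 and R² full = 0.2251, this is 0.1496/(0.7749/80), or 15.448 from unrounded values. The square of the demonstrator's t is also 15.448. The model comparison therefore repeats the planned t-test without its sign.

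**The word *isolate*.** Data Collection and Management (2.11) places the control period from May 2023 to January 2024 and starts the intervention phase in July 2024. The Discussion adds heightened awareness from study events and recruitment, and ward affiliation left out of the models. All of this sits in the same term as the demonstrator.

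**The case against.** The strongest reply is that direction is already in the plan. Each outcome has a regression with demonstrator use as a predictor, and the t-test of that predictor is a test of a signed, adjusted coefficient. A full-versus-reduced comparison is a conventional supplement to it. This stands in part. A reader might infer that the whole analysis cannot show whether the application saves or costs time; the document does not support that, because the coefficient is part of the planned model and its sign can be read. What remains is that the plan assigns the effect to the R² difference and gives the t-test significance only.

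A second reply is that coefficients and intervals are reporting detail that a condensed article may leave to a fuller document. That would answer a silence. Here the article makes an explicit choice of measure, and that choice does not fit its hypothesis.

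Two further readings are tempting and should not be drawn:

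- *That a later trial could not be planned from the result.* With the full-model R² it could: f² = ΔR²/(1 − R² full), which in the invented data is 0.1496/0.7749 = 0.193, an input for a regression power calculation. A coefficient in minutes is more useful, but the R² difference is not useless.
- *That differences between the phases are a reason to prefer the coefficient.* They affect the coefficient just as much. They bear only on the wording, and the Discussion already discloses them. The article also calls the study exploratory.

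**Conclusion.** The point holds for the quantity that the plan names. A difference in R² between nested least-squares models is non-negative, free of units, and equal for benefit and harm of the same size, so it cannot by itself answer a directional hypothesis. This follows from algebra and does not depend on the sample size, the group split or the covariates. The figure 0.059 does depend on d = ±0.5, a 50:50 split and no other predictors; the 0.150 comes from invented data and only illustrates the point.

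One assumption is that explanatory performance means R², as the same section suggests. If adjusted R² were meant, its difference could fall below zero when the term explains very little, but it would still be the same for a saving and a cost of equal size.

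The change should be made, because the stated effect measure does not match the question. It does not invalidate the planned models.

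**What to change.** In the Analysis Plan (2.12):

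1. State that, for each outcome, the effect estimate is the adjusted regression coefficient for demonstrator use with its 95% CI, in the outcome's own units: minutes for the durations, NASA TLX points for task load, points for guideline adherence.
2. Keep the difference in R² between the full and reduced models as a supplementary description of variance explained.
3. Replace the wording "using the difference in explanatory performance to isolate the effect attributable to the demonstrator use" with a statement that the model estimates an *adjusted difference between phases*, in line with the bias acknowledged in the Discussion.

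The cost is wording only. The coefficient and its interval come from the regression already planned in SPSS, with no new data, model or sample size.

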### Design

2.3

The study is designed as a monocentric, non‐randomized, controlled pilot intervention study with a pre‐intervention data collection period followed by a data collection period during the deployment of the AI‐based application (intervention) on the wards. Due to the nature of the intervention, it is not possible to blind either participants or observers.

In the pre‐intervention phase, we observe the wound care and documentation for PI and IAD according to hospital standards in the control group, using a standardized observation form, and survey the nurse using a standardized questionnaire (Figure 2). In the subsequent intervention phase, we train the nurses in the intervention group to use the AI‐based application, then observe and survey the wound care and documentation supported by the AI‐based application, consistent with the procedures used in the pre‐intervention phase (Figure 2). The reporting of the study protocol is based on the SPIRIT AI extension (Cruz Rivera et al. 2020).

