### Measures

2.10

The measures of this study include the duration of wound assessment, dressing change, and documentation; the task load of the nurse during wound care and documentation; guideline adherence; and the accuracy of the AI predictions of wound type and classification in the clinical setting.

The duration of wound assessment, dressing change, and documentation is monitored during observation using standardized start and endpoints. The start point is defined as the moment dressing removal begins. If no dressing is present, the start point is the initiation of the first hands‐on wound care activity after patient positioning, such as a finger pressure test, measurement, or wound disinfection. Preparations, including patient positioning and material preparation, or interruptions, such as retrieving supplies from outside the room or responding to calls from other patients, are not included in the measurement. Documentation duration is measured separately since it does not always occur immediately after treatment. The start point is either opening the digital wound documentation or connecting the camera to the computer, and the endpoint is when the wound documentation is saved. It is also recorded whether a wound photograph is taken and whether the last known values are transferred from the existing documentation.

Guideline adherence is assessed using a set of five criteria identified during an expert workshop as relevant for evaluating guideline adherence in the context of wound care for PI and IAD. These criteria are derived from the “Prevention and Treatment of Pressure Ulcers” guideline published by the European Pressure Ulcer Advisory Panel (European Pressure Ulcer Advisory Panel, National Pressure Injury Advisory Panel, & Pan Pacific Pressure Injury Alliance 2019).

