The selected criteria include performing a finger pressure test or the transparent disk method in the presence of redness (recommendation 9.1), accurately assessing wound type and classification (recommendation 9.2), applying wound edge protection in cases of macerated wound edges or surrounding skin (recommendation 3.1), and ensuring pressure relief for pressure injuries (recommendations 5.1 and 5.5). The response options for these criteria are binary: ‘No’ or ‘Yes or not required’. Sum scores are calculated from the responses, assigning a score of 1 to ‘Yes or not required’ and a score of 0 to ‘No’. Interrater reliability is also measured in the study. Additionally, the nurse's task load during wound assessment, dressing change, and documentation is evaluated using the standardized and validated NASA TLX questionnaire (Human Performance Research Group n.d.).

Other covariates measured include the nurse's professional experience, wound severity, and the general workload of the shift, which is assessed on a 5‐point scale relative to the average.

To assess the accuracy of the AI predictions of wound type and wound classification in the clinical setting, the wound is independently assessed on‐site by a member of the study team, separate from the nurse's assessment and the AI prediction. This assessment serves as the ground truth for calculating the accuracy of the AI predictions regarding wound type and classification.

Additionally, the usability of the documentation systems used, namely the standard clinical documentation systems and the AI‐based digital system, will be assessed in both the control and intervention groups. Usability will be evaluated using the two‐item UMUX Lite questionnaire with a 7‐point Likert scale (Lewis et al. 2013) because of its brevity (Borsci et al. 2020) and comparability with other studies and the SUS scale (Lewis et al. 2013).

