### Data Collection and Management

2.11

The pre‐intervention data collection period began in May 2023 and continued until the required sample size was reached in January 2024. Following the completion of AI development in the technical sub‐study, we began training nurses and initiated the intervention phase with the corresponding observations and surveys in July 2024. Observations, on‐site wound assessments, and surveys of the nurses are conducted by trained nursing scientists using a digital questionnaire on tablets through the Lime Survey tool (Limesurvey GmbH 2024). The collected data is anonymized and stored on secure, access‐restricted servers available only to the research team.

To ensure that the documentation created can be linked to the observations while maintaining data confidentiality and security, a unique identifier is generated in the AI‐based application and recorded on the observation sheet. Neither this ID nor the data collected during the wound documentation, observation, and survey can be used to identify the patient or nurse. All collected data is stored in a password‐protected folder accessible only to the study team. Consent forms and confirmation of receipt of the voucher are stored securely and are also only accessible to the study team. Upon completion of data collection, the data will be exported and statistically analyzed using SPSS version 28.0.0.0 (IBM Corp 2021). Given the study's small sample size, relatively low complexity, and clearly defined endpoints, the establishment of a data monitoring committee is not deemed necessary.

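### Kendall's tau, the only interrater statistic named, measures ordering and not agreement, so it can flatter the reliability of the guideline-adherence sum score

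*Protocol article*

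**What the plan says.** Section 2.10 (Measures) defines the endpoint: "Guideline adherence is assessed using a set of five criteria". On the item scale it says "The response options for these criteria are binary", and on the total, "Sum scores are calculated from the responses, assigning a score of 1" to a criterion that is met or not required, and 0 otherwise. The total therefore runs from 0 to 5. The same paragraph adds: "Interrater reliability is also measured in the study". It does not name the variable that is rated twice.

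Section 2.12 (Analysis Plan) fixes the method: "To analyze the interrater reliability of the observers, we will use Kendall's rank correlation coefficient", that is, Kendall's tau. It gives no variant of tau and mentions no kappa, intraclass correlation, percent agreement or between-observer difference. It also plans a linear regression of guideline adherence on use of the application.

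Two other statements give the context. Section 2.11 says that observations, on-site assessments and "surveys of the nurses are conducted by trained nursing scientists". Section 2.3 (Design) says "it is not possible to blind either participants or observers". The Discussion adds that no suitable instrument for adherence existed, so the criteria came from an expert workshop.

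**The concern.** A reliability analysis should show whether one observer can stand in for another. Here that means whether the two would record the same adherence score for the same wound-care episode. Tau answers a different question. It compares pairs of cases and counts how often both observers put them in the same order. Adding a constant to every score from one observer leaves every order unchanged, so tau does not move.

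The adherence analysis depends on the level of the score, because it compares a pre-intervention phase with an intervention phase. If one observer is more lenient, and the observer mix or an observer's behaviour changes between phases, the difference in leniency enters the estimated effect. The reliability analysis is where a reader would look for such a difference. Because the instrument is new, that analysis is also important evidence for the endpoint.

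**Working it through.** The article gives no reliability figure, number of double-rated cases or threshold, so there is nothing to reproduce. The check uses constructed ratings by two observers. Only the 0/1 item scale and the 0 to 5 range come from the document; all counts are assumptions.

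**Formulas.**
- tau-b = (C − D) / √[(P − Tₐ)(P − T_b)], where C and D are concordant and discordant pairs, P = n(n − 1)/2, and Tₐ and T_b are the pairs tied for each observer.
- Absolute-agreement ICC for two raters = (MSR − MSE) / [MSR + MSE + 2(MSC − MSE)/n], with mean squares for cases (MSR), raters (MSC) and residual (MSE).
- kappa = (pₒ − pₑ)/(1 − pₑ), with observed agreement pₒ and chance agreement pₑ.

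**1. Sum score, constant shift, 20 cases.**
- Observer A has scores 1 to 5 with counts 2/4/6/5/3, and B is always one point lower. C = 155, D = 0, P = 190, and 35 pairs are tied for each observer. tau-b = 155/√(155 × 155) = 1.00. Exact agreement is 0%. MSR = 3.005, MSC = 10, MSE = 0, so ICC = 3.005/(3.005 + 2 × 10/20) = 0.75.
- A has scores 2 to 5 with five cases each, and B is always two points lower. tau-b is again 1.00 with 0% exact agreement. MSR = 2.632, MSC = 40, MSE = 0, so ICC = 2.632/(2.632 + 2 × 40/20) = 0.40.

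**2. Sum score with a ceiling, 40 cases.** The stricter observer has scores 0 to 5 with counts 0/1/4/10/15/10. The lenient one gives one point more, up to the maximum of 5.
- The observers match only on the ten cases that the stricter one scored 5: 10/40 = 25%.
- P = 780, C = 429, D = 0, ties 201 and 351. tau-b = 429/√(579 × 429) = 0.86.
- MSR = 1.595, MSC = 11.25, MSE = 0.096. ICC = 1.499/(1.691 + 2 × 11.154/40) = 1.499/2.249 = 0.67.
- The mean difference is 30/40 = 0.75 points.

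With more cases near the ceiling (counts 0/0/2/8/15/15), tau-b is 316/√(541 × 316) = 0.76 and exact agreement is 15/40 = 37.5%.

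**3. One binary criterion, 40 pairs.** The order of the counts is both yes / A only / B only / both no. For 2×2 data tau-b equals phi.

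| Table | pₒ | pₑ | kappa | phi = tau-b |
|---|---|---|---|---|
| 20/12/0/8 | 28/40 = 0.70 | 0.8 × 0.5 + 0.2 × 0.5 = 0.50 | 0.20/0.50 = 0.40 | 160/√(32 × 8 × 20 × 20) = 0.50 |
| 10/20/0/10 | 20/40 = 0.50 | 0.75 × 0.25 + 0.25 × 0.75 = 0.375 | 0.125/0.625 = 0.20 | 100/√(30 × 10 × 10 × 30) = 0.33 |

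Listing every 2×2 table with 20 pairs in which both observers vary shows none with tau-b = 1 and any disagreement. If either observer gives the same answer throughout, the denominator is zero and tau-b is undefined, even when the observers agree on every case. That could arise here, because a criterion that does not apply also scores 1.

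**The case against.** The strongest reply has four parts.

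**Limiting case.** The combination of 1.00 and 0% needs a stricter observer who never awards the top score. This stands. The capped examples are more realistic and give 0.86 and 0.76, not 1.00. Tau still looks much better than the 25% and 37.5% exact agreement beside it.

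**Binary data.** A reader might infer that tau can be perfect without any agreement on every variable, or that it has no meaning for pressure injury against IAD. Neither is right. Both the single criteria and wound type have two categories, where tau-b is phi, has a clear meaning, and reaches 1 only with full agreement. Random disagreement and one-sided bias both lower it.

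**Scope.** A reader might extend the point to the durations and to the on-site assessment used as ground truth for AI accuracy. A constant or proportional timing difference would indeed leave tau at 1.00, but the article nowhere says that these variables are rated twice. The reliability sentence in Section 2.10 directly follows the adherence score.

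**Consequence.** A reader might infer that observer differences do bias the before-after comparison. That needs a change in observer mix or behaviour between phases, which the article does not report. Nor would better statistics solve the lack of blinding: two unblinded observers with the same expectation agree with each other, and kappa and ICC miss that as tau does.

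It is also fair that reliability enters no effect estimate or test, and that the study is an exploratory pilot which already lists consecutive groups and lack of blinding as limitations. This limits the weight of the point but does not make tau an agreement measure. The statistic is stated in the text, so the point is not about a detail left to another document.

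**Conclusion.** The point holds for the guideline-adherence sum score: the stated statistic does not measure what it is meant to show. It ignores a constant level difference between observers entirely (1.00 with 0% exact agreement) and understates one that is cut off by the ceiling (0.86 with 25% exact agreement and ICC 0.67). For single criteria the defect is milder: an overstatement of about 0.10 to 0.13 against kappa in the two tables shown, and no value at all when an observer is constant.

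The sizes rest on constructed ratings and illustrate a property of tau; they do not predict what these observers will show. The practical risk is false reassurance about a new, observer-scored endpoint. Reliability is a supporting analysis, so the planned effect estimates stay as they are. The change should be made, but the main analyses do not depend on it.

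**What to change.** Replace the tau sentence in Section 2.12 with agreement statistics on the existing double-rated observations, each with a 95% confidence interval, and name the variables that were rated twice:

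- each binary criterion: Cohen's kappa and percent agreement;
- sum score: absolute-agreement ICC (or weighted kappa) and the mean between-observer difference;
- only if they were also double-rated: kappa for wound type, weighted kappa within each ordered classification scale, and absolute-agreement ICC for durations.

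Percent agreement covers criteria on which an observer never varies. The mean difference shows leniency directly, in score points.

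The cost is one sentence. The paired ratings are the same, no new data are needed, and the planned software can do the work. The only downside is that the reported reliability may look less favourable.
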